#### Process measures

Moderators: depression severity (PHQ9), age of onset (MINI), number of episodes (MINI), LTC and socioeconomic status will be collected at baseline interview. Mediators: number of contacts, level of activation using the Behavioural Activation for Depression Scale (BADS) collected at treatment sessions [25].

Baseline demographic measures: DOB, ethnicity, education level, socioeconomic status and sex.

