**External pilot study:**

Objectives:Quantify the flow of participants (eligibility, recruitment and follow-up rate)Evaluate proposed recruitment, assessment and outcome measure collection methodsExamine the delivery of the enhanced support intervention in a community pharmacy setting (intervention uptake, retention and dose) to inform process evaluationProcess evaluation, using semi-structured interviews with participants across a range of socio-economic settings, and pharmacy staff to explore the acceptability of the ESI within community pharmacy, elements of the intervention that were considered useful (or not) and appropriateness of study procedures

Design: Pilot randomised controlled trial, including a prospective economic and qualitative evaluation

Setting: As above

Population: As above

Intervention: As above with adaptations post feasibility study

Comparator: Usual care

Sample size: 100 participants

Outcomes: Data will be used to estimate recruitment, intervention delivery and study completion rates as per objectives 2a–d. Definitive estimates of the effectiveness of ESI will not be made.

Primary outcome: Depression severity (Patient Health Questionnaire 9) at four months.

Secondary outcomes: Patient acceptance, uptake and attrition. ICD10 depression status, anxiety (GAD 7), health-related quality of life (SF-12v2) and health-state utility (EQ5D 3L) will be measured at four months.

Economic evaluation: The incremental cost per QALY will be calculated from both the NHS and societal perspective.

Process evaluation: Using mixed methods, potential mediators/moderators of the intervention, the acceptability (to participants and pharmacy staff), barriers and facilitators to the use of ESI in community pharmacy, and impact on usual practice will be examined. Semi-structured interviews with approximately 30 study participants, 20 pharmacy staff and eight GPs near participating pharmacies will be conducted.

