## Methods—feasibility study

### Design

A case series study with nested qualitative evaluation.

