### Outcome measures

Depression severity will be measured by the Patient Health Questionnaire 9 (PHQ9) [19]. Widely used in clinical trials and settings, the PHQ9 provides excellent internal and external validity and specificity/sensitivity in a UK population [20]. The PHQ9 would be the primary outcome measure in a definitive RCT.

Secondary outcome measures will include prevention of depression (PHQ9 less than 10), anxiety (GAD7) [21], somatic symptoms (PHQ15) [22], quality of life (SF-12v2) [23], health-state utility (EQ5D-3 L) [24] and healthcare utilisation via an adapted version of the Adult Service Use Schedule (AD-SUS).

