### Assessment and follow-up

Data will be collected at screening/eligibility, baseline and four  months post-baseline. Due to the nature of the feasibility study, blinding to allocation is not possible.

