### Outcome measures

As described in the feasibility study above but with the exclusion of the PHQ15.

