### Comparator

The control group will be the usual primary care management of sub-threshold depression and other local community provision.

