### Process evaluation

As per UK MRC recommendations, a mixed methods approach to process evaluation [33] will be used to consider fidelity, implementation, mechanisms and context. Descriptive statistics will be used to describe elements of the intervention (participants, dose and intervention content). The moderational analysis will examine baseline variables that may moderate outcomes such as age, depression onset age, number of episodes and socioeconomic status. The mediational analysis will investigate hypothesised mechanisms of change such as number of sessions, content of scheduled contacts (from pharmacy ESI facilitator records) and changes in activation (BADS) using established methodology [34]. As this is an external pilot RCT, it is considerably underpowered to undertake these evaluations so data will be summarised and used to refine process evaluation design to inform a future large-scale definitive RCT.

A process evaluation using qualitative methods will be used to explore acceptability and important elements of the intervention from the perspective of the participants. A purposive sample of approximately 15 participants who completed the intervention will be invited to participate in a semi-structured interview (recruitment and data collection will continue until category saturation has been achieved). Sampling will ensure that participants with a range of age and gender are sampled and from a range of socio-economic groups. The interviews will explore the acceptability of case-finding for sub-threshold depression, receiving the enhanced support intervention (ESI) within a community pharmacy setting, impact on relationship with general practice and research procedures. A sample of participants who dropped out (had less than two sessions) will also be invited to participate in a semi-structured interview to explore reasons for drop out. It is likely approximately 15 interviews will be needed to achieve data saturation [35].

Sampling will be ensured in areas of higher deprivation (i.e. bottom two quintiles of index of multiple deprivation (IMD)), to enable us to explore perspectives of people particularly from lower socioeconomic status (SES). Perceptions of the appropriateness of the intervention for people with poor health literacy and from lower socioeconomic status (SES) will be explored. All interviewees will be interviewed at a time and place convenient to them (e.g. at home, in the pharmacy, GP surgery or by telephone).

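### BADS is scheduled only at ESI sessions, so the pilot's mediational analysis cannot estimate the effect of allocation on activation

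*Protocol article*

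**What the plan says.** The feasibility methods, under Process measures, give each group of process variables its own collection point. Moderators are taken at the baseline interview. For mediators the text is: "Mediators: number of contacts, level of activation using the Behavioural Activation for Depression Scale (BADS) collected at treatment sessions". This was written for a single-arm design: "A case series study with nested qualitative evaluation".

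Process measures is a subsection of Outcome measures. The pilot's Outcome measures section carries that material over in one line: "As described in the feasibility study above but with the exclusion of the PHQ15". It makes no change to BADS.

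The questionnaire measures listed under Outcome measures are the PHQ9, GAD7, PHQ15, SF-12v2, EQ5D-3L and an adapted service-use schedule. BADS is not among them. The assessment points are stated as: "Data will be collected at screening/eligibility, baseline and four months post-baseline".

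The pilot's comparator is usual care: "The control group will be the usual primary care management of sub-threshold depression and other local community provision".

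The pilot's Process evaluation section says: "The mediational analysis will investigate hypothesised mechanisms of change such as number of sessions, content of scheduled contacts", and adds changes in activation on BADS. It then notes that the pilot is far too small for these evaluations, so the data will be summarised and used to refine the process evaluation of a definitive trial. The abstract likewise says the process evaluation will examine "potential mediators/moderators of the intervention, the acceptability (to participants and pharmacy staff), barriers and facilitators".

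**The concern.** Mediation of a randomised effect has two links: allocation to mediator, and mediator to outcome. The first can be estimated only if the mediator is measured in both arms. A measure taken at treatment sessions exists only where there are sessions, which here means the ESI arm. The schedule suits a case series but was carried into a two-arm trial without adjustment.

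At stake is what the pilot can teach about the process evaluation. Without control-arm BADS it cannot show how far activation differs between arms, or separate change under ESI from change that would have happened anyway. Nor can it show whether control participants will complete the scale. These are inputs that a definitive trial's mediation design would need, and refining that design is the stated use of the data.

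**Working it through.** **1. The plan's own figures.** The Sample size section assumes 20% loss from 100 and gives ± 8 points. The Wald half-width is 1.96 × √(0.20 × 0.80 / 100) = 0.0784, giving 12.2% to 27.8%, so the figure reproduces. Measured participants: 100 × (1 − 0.20) = 80, or 40 per arm under the 1:1 allocation of 50 and 50. The present point does not depend on these figures; they set the scale for step 4.

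**2. Where each named mediator exists in the pilot, as described.**

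| Variable | ESI arm (50) | Control arm (50) |
|---|---|---|
| BADS | at sessions attended | no value |
| Number of sessions | observed | zero by design |
| Content of contacts | from facilitator records | undefined |
| Any of these before randomisation | none stated | none stated |

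The last row follows from the Randomisation section: allocation comes after the baseline interview, and sessions come later still.

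**3. Is the allocation-to-BADS path estimable?** The model is BADS = i + a × arm + error. If every participant with BADS data has arm = 1, the intercept column and the arm column are identical. The design matrix [1, arm] then has rank 1 where 2 is needed (checked numerically with 40 ESI rows), so *a* is not identified. More participants on the same schedule add more rows of the same kind, so sample size does not help.

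Two further consequences follow within the ESI arm. A session-based change score needs at least two sessions, while the Process evaluation section defines drop-outs as those with fewer than two, so they can have no change score. And a first value taken at a session is a post-randomisation value.

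**4. What BADS in both arms would give (40 per arm measured).** The article gives no BADS effect size, so the effects below are assumptions, in SD units.

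- 95% CI half-width for the between-arm difference: 1.96 × √(2/40) = 0.44 SD.
- Difference detectable with 80% power: (1.96 + 0.84) × √(2/40) = 0.63 SD.
- Power for the allocation-to-BADS path: Φ(0.3/√(2/40) − 1.96) = 27% at 0.3 SD, and Φ(0.5/√(2/40) − 1.96) = 61% at 0.5 SD.
- Power for both paths jointly, by simulation (2,000 runs, total 80, assumed mediator-to-outcome slope 0.3): about 19% and 43% for the same two effects.
- Control-arm completion rate, if 80% of 50 complete: half-width 1.96 × √(0.80 × 0.20 / 50) = 0.11, or ± 11 points.

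The path becomes estimable but stays imprecise. The gain is in design inputs (mean, SD, completion, a rough difference), not in a test.

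**The case against.** The strongest reply is that the article plans no mediation inference. The Process evaluation section says the data will be summarised and used for design, and session counts, contact content and activation within the ESI arm can all be summarised as collected. This stands, and it limits the severity. A reader might infer that the mediational work cannot be done at all. The documents do not support that, because within-arm description and within-arm associations with the PHQ-9 remain possible, although they are not mediation of the randomised effect. But the caveat is about power. It does not say that one arm lacks the mediator, and a BADS summary by arm is impossible on the stated schedule.

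A second reply is that session-only collection in the pilot is inferred from a single-arm section through a one-line cross-reference, and that the full protocol, not shown, may schedule BADS in both arms. That is possible. Still, the article states a collection point for BADS rather than leaving it out, sets it against a different one for moderators, and changes only the PHQ15 for the pilot. If the full protocol differs, the article misdescribes it and a sentence of correction is needed.

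A third reply is that not every mediator is missing in controls. This is right: the number of sessions there is a known zero. The problem with session number and content is that they measure dose, not that data are absent.

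A reader might also infer that the definitive trial would inherit the schedule. The article says its process evaluation will be refined, so that does not follow. Nor can the number of ESI participants without a change score be read from the article: its 20% is loss to follow-up, not session drop-out.

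**Conclusion.** The point holds in a limited form. As described, BADS is available for 0 of 50 planned controls and before randomisation for no one. The effect of allocation on activation, and hence an indirect effect through it, cannot be estimated, and the pilot yields no control-arm BADS mean, SD or completion rate. Session number and contact content describe dose in the ESI arm.

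This rests on reading the pilot's cross-reference as carrying the BADS timing over unchanged, which is what the article says; the full protocol could show otherwise.

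Severity is low to moderate. Participant flow, recruitment, attrition, the PHQ-9 SD, the PHQ-9 comparison and the economic analysis are untouched, and no mediation conclusion is planned.

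**What to change.** - Collect BADS at baseline (before randomisation) and at four months in both arms. Keep session-level BADS for the ESI arm.
- Summarise BADS change by arm, with completion rates. For participants already past baseline, report four-month BADS by arm only, since they can have no change score from baseline.
- Describe number of sessions and contact content as dose, summarised in the ESI arm.
- Reconcile the Process measures, pilot Outcome measures and Process evaluation sections so that all three state the same schedule.
- If BADS cannot be added, call the analysis a description of activation within the ESI arm.

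The cost is one short questionnaire at two contacts that already take place, plus a minor amendment. The CHEMIST study status section says recruitment was still open at the time of writing; if it has since closed, relabelling is the practical option.

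Two limits remain after the change. Four-month BADS is concurrent with the four-month PHQ-9, so temporal order from mediator to outcome is not established. And precision at about 40 per arm stays limited, so the results should be presented as design inputs.

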### Assessment and follow-up

Data will be collected at screening/eligibility, baseline and four  months post-baseline. Due to the nature of the feasibility study, blinding to allocation is not possible.

### Sample size

No formal sample size calculation has been undertaken for the feasibility study. A sample size of 20–30 participants recruited will be sufficient to meet feasibility phase objectives.

### Outcomes and data analysis

As this is the feasibility phase, study implementation (recruitment and attrition rates, quality of data collection) will be assessed at baseline and four months, along with ESI adherence (number of contacts, DNA and drop out), as per the feasibility objectives. Rates will be reported descriptively.

### Qualitative evaluation

In-depth interviews will be conducted with up to ten patient participants (purposively sampled across pharmacy location and with a mix of LTCs, from different areas of deprivation) to explore the acceptability of the content and location of the ESI. Interviews with approximately ten ESI facilitators will be conducted following training and again at the end of the feasibility study. A focus group will be conducted with pharmacy staff to explore the feasibility and acceptability of the training, intervention and study procedures.

Existing literature will be used to develop topic guides. The Normalisation Process Theory (NPT) approach [26] will be used to sensitise topic guides and provide a framework for analysis and interpretation of data in order to identify the barriers and facilitators to implementation. This approach has been used in previous studies [27].

The analysis will inform adaptations to the intervention materials, training and study procedures for the pilot RCT.

### Qualitative evaluation recruitment

Recruitment of patient participants for qualitative interviews will be included in the information and consent process for the feasibility study.

Staff involved in CHEMIST particularly ESI facilitators will be contacted directly by the study team by letter and provided with the staff participant information sheet and consent form. They will be provided with pre-paid envelopes to return the documentation directly to the study team. This process will be carried out independently of the pharmacy to ensure it is free from coercion from employers or co-workers. All data collected will be anonymised by the qualitative research team prior to reporting to ensure the confidentiality of participants.

## Methods—external pilot study

### Design

An external pilot RCT including nested process evaluation and economic evaluation.

### Setting

Community pharmacies in the North of England sampled across quintiles of area-level deprivation.

### Study population

As described in the feasibility study above.

### Recruitment

Recruitment methods will include those described in the feasibility study above, but with refinements following learning from feasibility phase.

### Outcome measures

As described in the feasibility study above but with the exclusion of the PHQ15.

### Assessment and follow-up

Participants will be offered the option of completing baseline and follow-up questionnaires over the telephone or via post. Due to the nature of the study, participants and those delivering the intervention will be unblinded to allocation. Researchers carrying out follow-up assessments will be blinded to treatment allocation.

### Intervention

As described in the feasibility study above but with adaptations made following the feasibility study.

### Comparator

The control group will be the usual primary care management of sub-threshold depression and other local community provision.

### Sample size

Sample size calculations are based on estimating attrition and the standard deviation of the primary outcome. Assuming 20% of participants are lost to follow-up with a sample size of 100, then the 95% confidence interval for this level of attrition will be the observed difference ± 8 percentage points (i.e. between 12 and 28%) (%) [28]. Hence, an external pilot trial of 100 participants should ensure robust estimates of recruitment and follow-up in this population. Furthermore, an external pilot study of 80 measured subjects will provide robust estimates of the standard deviation of the outcome measure in this population to inform the sample size calculation for a subsequent larger definitive fully powered trial [29].

### Randomisation and allocation concealment

Individual independent randomisation will be used. Randomisation will be carried out by the York Trials Unit (YTU), University of York, online randomisation service (URL:www.yorkrand.com/), independently of the trial team. One hundred participants will be randomised on a 1:1 basis to either the intervention group (50) or control group (50) following completion of the baseline interview.

### Outcome and data storage and analysis

Outcome data will be stored securely at the Department of Health Sciences, University of York, following strict confidentiality and data storage standard operating procedures (SOPs) and protocols. Pilot RCT data will be scanned and validated at the York Trials Unit as defined by YTU SOPs and protocols. Data will be stored on the YTU system and will be the responsibility of the University of York and sponsor (TEWV NHS FT) as set out in a collaboration agreement. Requests for access to data will be considered in line with YTU and sponsor SOPs.

The flow of participants through the trial will be detailed in a CONSORT flow diagram (see Additional file 1). The number of people screened, randomly assigned, receiving the intervention, completing the study protocol and providing outcome data will be summarised overall and by trial arm. The number of individuals withdrawing from the intervention and/or the trial and any reasons for withdrawal will be summarised by trial arm. To quantify the acceptability of the intervention, the number of sessions attended will also be summarised. The primary outcome of this study will be reported descriptively by treatment arm using mean, standard deviation (SD), 95% confidence intervals, median and 25th and 75th percentiles.

While the main aim of this study is to establish practicality, feasibility, recruitment rates and key parameters for the sample size in order to inform a full-scale trial, and although it is unlikely that the small sample size will result in effectiveness being established, we will none the less test the primary outcome to mimic practice for full-scale trial. Results from this analysis will be treated as unreliable and interpreted with caution [30, 31].

The two groups will be compared for the primary outcome (PHQ-9 at 4 months follow-up) using linear regression with adjustment for important baseline covariates. Estimates from the model and 95% CI will be presented. We may also explore the impact of pharmacy effects. The potential impact of ‘pharmacy effects’ will be quantified using intraclass correlation coefficient (ICC) estimates with 95% confidence intervals and the average caseload per pharmacy ESI facilitator. All secondary outcomes will be summarised descriptively by treatment arm using mean, SD, 95% confidence intervals, median, 25th and 75th percentiles for continuous outcomes, and the number of events and percentages for categorical data.

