### Recruitment

Recruitment to sub-threshold depression studies within community pharmacy is untested in the UK. Therefore, a key objective of the feasibility study will be to refine potential recruitment approaches to test in the external pilot RCT. Three approaches will be used.Pharmacy recruitment. Potential participants will be identified via medication use linked to LTC and/or other pharmacy use. They will be provided with a study information pack either directly, attached to home delivery prescriptions or via pharmacy mail outs.Publicity recruitment. Posters will be placed in community pharmacies, general practices and local community settings advertising the study with a central contact point for the study team. Interested people will be invited to contact the study team either by phone, email or via the study website.Primary care recruitment. General practice (GP) database searches will be used to identify potential participants (those with one or more LTC) and the study information pack will be mailed out by the practices.

The study information pack will include an invitation letter, a participant information sheet, a consent form, a background information sheet and a stamped addressed envelope for return to the study team.

These procedures will be refined in the feasibility phase to facilitate use and evaluation in the pilot RCT.

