The ESI will be delivered by pharmacy support staff (ESI facilitators) experienced in the delivery of extended roles (such as smoking cessation using behavioural change approaches) and/or training to Royal Society of Public Health standard (Understanding Health Improvement Level 2). Fidelity will be supported by ESI facilitator manuals and comprehensive face-to-face training adapted from those used in previous studies. In addition, a bespoke competency assessment will be used (based upon experience from previous studies) at the end of the intervention training to ensure ESI facilitators are able to support participants in the intervention. With participant consent, audio recordings of the intervention support sessions will be undertaken. A random selection of recordings (10–20%) across the different phases of the intervention (early/late) will be collected from each ESI facilitator and independently reviewed.

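### The primary PHQ-9 regression has no term for ESI participants sharing a facilitator, and the planned ICC is not tied to the same unit as the caseload or to an arm

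*Protocol article*

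**What the plan says.** All references are to the Protocol article, external pilot methods unless noted.

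- **Allocation** (Randomisation and allocation concealment): "Individual independent randomisation will be used", 1:1, 50 per arm.
- **ESI arm** (Intervention, described under the feasibility study and carried over to the pilot with adaptations): "The ESI will be delivered by pharmacy support staff (ESI facilitators) experienced in the delivery of extended roles".
- **Control arm** (Comparator): "The control group will be the usual primary care management of sub-threshold depression and other local community provision". Controls have no facilitator.
- **Primary model** (Outcome and data storage and analysis): the arms are compared on PHQ-9 at 4 months "using linear regression with adjustment for important baseline covariates". "Estimates from the model and 95% CI will be presented". No facilitator or pharmacy term is named.
- **Clustering** (same section): "We may also explore the impact of pharmacy effects". The next sentence is firmer. It says the potential impact will be "quantified using intraclass correlation coefficient (ICC) estimates with 95% confidence intervals and the average caseload per pharmacy ESI facilitator".
- **Status of the comparison** (same section): it is run to rehearse the full-scale trial, and its results are to be treated as unreliable. The section also lists parameters for the full trial's sample size among the main aims.

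**The concern.** Individual randomisation with shared therapists in one arm is a partially nested design. ESI outcomes can be correlated within facilitator, and control outcomes cannot be correlated by that route. A regression that treats all participants as independent then understates the standard error of the difference between arms.

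The planned clustering outputs are also loosely fixed. The ICC is labelled as a pharmacy effect, the caseload is per facilitator, and the arm is not given. A design effect needs the ICC and the cluster size at the same level. Exploring pharmacy effects is optional in one sentence, and quantifying them is promised in the next.

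Two things are at stake: the width of the CI that the pilot will present, and whether the ICC and caseload can be used together to size the definitive trial.

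**Working it through.** **The plan's own figure.** Under Sample size, the stated precision for 20% attrition with n = 100 is ±8 points. Check: 1.96 × √(0.2 × 0.8 / 100) = 0.0784, giving 12.2% to 27.8%, which rounds to the stated 12% to 28%. Measured participants: 100 × 0.80 = 80. These figures reproduce and are not affected by this point. No design effect, ICC, caseload or power is stated, so there is no clustering figure to reproduce.

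**Inputs**
- From the document: 80 measured, hence 40 per arm if loss is equal.
- Assumed, because the document does not give them: facilitator ICC 0 to 0.10; measured caseload per facilitator m from 1 to 10; one or two facilitators per pharmacy; equal total variance in the two arms; normal approximation.

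**Formulas**
- ESI-arm design effect: DE = 1 + (m − 1) × ICC
- True SE / unadjusted SE = √((1 + DE) / 2), because only one of two equal arms is inflated
- True coverage of the nominal 95% CI = 2Φ(1.96 / ratio) − 1

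**Effect on the CI**

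| ICC | m | DE (ESI arm) | SE ratio | CI too narrow by | Coverage |
|---|---|---|---|---|---|
| 0, or any ICC with m = 1 | – | 1.00 | 1.000 | 0% | 95.0% |
| 0.01 | 5 | 1.04 | 1.010 | 1.0% | 94.8% |
| 0.02 | 5 | 1.08 | 1.020 | 1.9% | 94.5% |
| 0.05 | 5 | 1.20 | 1.049 | 4.7% | 93.8% |
| 0.05 | 10 | 1.45 | 1.107 | 9.6% | 92.3% |
| 0.10 | 10 | 1.90 | 1.204 | 17.0% | 89.6% |

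Example, ICC 0.05 and m = 5: DE = 1 + 4 × 0.05 = 1.20; ratio = √(2.20 / 2) = 1.049; 1.96 / 1.049 = 1.87; coverage 93.8%.

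**Effect of mixing levels.** Take an ICC of 0.05 estimated at pharmacy level and a facilitator caseload of 5.
- One facilitator per pharmacy: both cluster sizes are 5, DE = 1.20 either way, no error.
- Two per pharmacy: with the facilitator caseload, DE = 1 + 4 × 0.05 = 1.20. With the pharmacy's ESI total of 10, DE = 1 + 9 × 0.05 = 1.45.

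**Unequal caseloads.** DE = 1 + ((CV² + 1)m − 1) × ICC. With m = 5, ICC 0.05 and CV 0.7: 1 + (1.49 × 5 − 1) × 0.05 = 1.32, against 1.20 from the mean alone.

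**Precision of the ICC.** With 8 facilitators × 5 participants, the SE of an ICC of 0.05 is √(2 × 0.95² × 1.20² / (5 × 4 × 7)) = 0.14. The pilot estimate will be very imprecise.

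**The case against.** The strongest reply is that clustering has not been overlooked. The paragraph that names the regression also promises an ICC with its 95% CI and the facilitator caseload. The comparison is declared unreliable, definitive effectiveness estimates are ruled out in the abstract, and the sample size rests on attrition and SD. This stands, and it limits the consequence. It does not add a facilitator term to a model meant to rehearse the full trial, nor does it fix the unit of the ICC.

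The larger effects above also need large caseloads. The only hint of facilitator numbers is the roughly ten to be interviewed in the feasibility phase. If the pilot had ten, 40 measured ESI participants would mean m = 4. At ICC 0.05 that gives DE 1.15, an SE ratio of 1.04 and coverage of about 94.1%. This also stands: the likely effect is small.

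A reader might infer three stronger things that the document does not support.

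- *The CI is too narrow, without condition.* It is so only if the facilitator ICC exceeds 0 and caseload exceeds 1. A pharmacy effect shared by both arms, with allocation balanced within pharmacy, works the other way: √(1 − 0.05) = 0.975 at ICC 0.05.
- *The ICC is computed at pharmacy level over both arms, so controls dilute it.* The article names neither the arm nor the unit beyond a label it puts in quotation marks. Recruitment routes such as "General practice (GP) database searches will be used to identify potential participants" show that a control need not have come through a pharmacy, but say nothing about how the ICC is estimated. A facilitator-level ICC in the ESI arm fits the text equally well.
- *The design effect handed to the definitive trial is wrong.* None is stated or calculated, and with one facilitator per pharmacy the two levels coincide.

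The degrees-of-freedom method and similar detail would normally sit in the SAP, which is not shown and may settle these points.

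**Conclusion.** The point holds in a limited, conditional form. The stated primary model leaves out the one-arm nesting that the design creates, and the two clustering quantities are not tied to one unit or to an arm.

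For ICC up to 0.05 and caseload up to 10, the presented CI would be 0 to about 10% too narrow, with coverage between 95% and 92.3%. The ICC 0.10, caseload 10 case (89.6%) is an outer bound that nothing in the document points to. The mismatch of 1.20 against 1.45 arises only with several facilitators per pharmacy and an ICC estimated at pharmacy level. All these sizes rest on assumed ICCs and caseloads, equal loss and equal variances.

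No decision within the pilot turns on this CI. The point is worth acting on because the analysis is a rehearsal for the full trial and is meant to supply planning parameters for it.

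**What to change.** 1. Keep the linear regression, and prespecify alongside it a partially nested mixed model: a facilitator random effect in the ESI arm only, controls as singletons, and small-sample degrees of freedom (Satterthwaite or Kenward-Roger). Report its 95% CI next to that of the regression. If the variance component is estimated at zero, fall back on the regression and say so.
2. State that the ICC is estimated within the ESI arm at facilitator level, with its 95% CI.
3. Report the mean and the CV of caseload per facilitator, so that both quantities are at the same level.
4. Make the examination of clustering a commitment, replacing *may also explore* with *will*, so that the two adjacent sentences agree.

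The cost is a few sentences and one extra model. It needs the facilitator recorded for each ESI participant. The CI will be slightly wider, and the variance component will be imprecisely estimated at this sample size. That imprecision is the reason to place the nested model beside the regression and not in its place.
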